**4.6 The intervention**

*The training of peer educators*

Peer educators receive a standard training programme that is delivered by an external team of peer trainers with expertise in sexual health promotion. The training takes place in the Spring term (and the delivery of the programme in the following Summer term). All male and female Year 12 students (16/17 years old) in each experimental school are eligible to volunteer to undertake this training and participants receive accreditation from the University of London acknowledging their involvement in the programme. The training programme comprises a series of weekly meetings in which the peer educators are given information about sexual health issues and the opportunity to experience and develop participatory learning strategies and activities (i.e. role-play, use of quizzes, games, managing discussions, etc.). Peer educator training culminates in a workshop over two consecutive days which focuses on knowledge about relationships, contraception and sexually transmitted infections and techniques of classroom management and group facilitation. Peer educators either collect or are provided with information about local sexual health services. Emphasis is placed on training peer educators through techniques which they can adopt in the intervention. The aim is develop classroom strategies, appropriate to the age and experience of students in the intervention group, through which their communication and negotiation skills in relation to sexual behaviour and relationships will be enhanced. The content and delivery of the peer educator training is standardised as far as possible across the experimental schools. Training meetings are observed by members of the researcher team and peer educators participate in a questionnaire survey prior to the training. This survey is repeated after delivery of the intervention and focus group discussions undertaken with the peer educators .

##### *The delivery of the peer-led sex education programme*

The peer-led sex education programme is delivered in the Summer Term. It comprises three classroom sessions each lasting a minimum of one hour. The sessions focus on relationships, contraception and sexually transmitted infections, in order to match the objectives of the intervention to the endpoints of the trial (see above). Sessions may be timetabled in a variety of subject areas in accordance with the usual school practice for sex education provision. They are delivered by mixed sex teams of peer educators who deliver all three sessions to one group of students from Year 9. Teachers are not in attendance in the classroom during the sessions. Peer educators adopt a less formal role and approach than teachers and make more use of participatory classroom teaching techniques. These involve games and small groupwork, discussions, brainstorms, role-playing and demonstrating how to use condoms. The approach emphasises development of skills for sexual negotiation as well as knowledge about pregnancy, contraception, sexually transmitted diseases and the use of sexual health and contraceptive services. The organisation of the intervention their content and delivery is standardised as far as possible across the experimental schools.

**Table I Timing of research activities in relation to the intervention**

| Research Activities | | Intervention | |
| --- | --- | --- | --- |
| Experimental schools | Control schools |
| Autumn 1997 | - **Baseline questionnaire to yr9** |  |  |
| Spring  1998 | - Observation of recruitment - Baseline questionnaire with all peer educators - **Interviews with teachers** | Recruitment of peer educators | Continue with sex education as planned |
| Summer 1998 | - Observation of pre training and training sessions - **Observation of sex education sessions delivered to yr9*** - Follow up questionnaire with all peer educators - **Focus groups with yr9 students** - Focus groups with peer educators | Preparatory sessions with peer educators  Needs assessment by peer educators with yr9.  Training of peer educators  Delivery of sex education classes | Continue with sex education as planned |
| Autumn 1998 | - **Baseline questionnaire to yr9** - **Follow up questionnaire to yr10** |  |  |
| Spring  1999 | Repeat all of above for cohort 2 | | |
| Summer 1999 |
| Autumn 1999 | - **2nd follow questionnaire to yr11** - **Follow up questionnaire to yr10** |  |  |

* sex education in control schools is observed through out the year and depends on the timing of delivery which is decided by individual schools.

**Note: All activities in bold were carried out in both experimental and control schools. Others were carried out only in experimental schools**.

**5 Plan of investigation**

**5.1 Trial register and assignment of ID codes**

The trial register is composed of all pupils enrolled in year 9 at the time of the baseline survey. Each pupil on the trial register is assigned a unique ID code, composed of 8 characters. The ID code consists of a two figure code for the school (01 to 28) a single digit for the Year 9 cohort (1 or 2) a three figure code for the pupil (001 to 900) and a check letter at the end.

**5.2** **Survey Methods**

In phase I, questionnaire surveys are carried out in the classroom at baseline (pre-intervention), at 6 and 18 months post intervention for the two successive Year 9 cohorts. The questionnaires include measures of knowledge, attitudes, self-efficacy, sexual behaviour including vaginal intercourse, condom and contraceptive use, and views on any previous sex education. The questionnaires were developed and piloted in consultation with students, and include space for comments. Where possible, a member of the research team is present to explain the purpose of the questionnaire, reassure students about the confidential nature of their responses and answer any queries. In phase II, postal questionnaires, together with a urine or saliva “home testing kit” will be sent to all pupils on the trial register who give consent to be approached by the research team after they have left school.

**5.3 Process evaluation**

Extensive process evaluation is an integral part of the research design. The primary aims of this are: to document how the intervention is implemented in the experimental schools, and what kind of sex education is provided in control schools; to collect information from all the study schools about the experience and impact of taking part in the RIPPLE study; to examine the extent to which sex education in control schools may have been 'contaminated' by knowledge about the peer-led programme and to collect data on the key processes involved in the provision and receipt of peer-led sex education which can then help to interpret outcome data. Information is gathered about all key events in the implementation of the peer-led intervention in all experimental schools. Information about the sex education curriculum is collected from all control schools, while observation and focus groups are carried out in a 50% random sample of control schools. In addition, information is colllected about the school environments in which the trial is taking place. For example, the quality of relationships between staff and students and the status of the school within the community are assessed. Some process information is gathered within the questionnaire survey. However most of it is obtained by using other methods, including focus groups, interviews with staff and observations of peer educator training and delivery of the intervention.

*Focus groups*

Focus groups are carried out with single sex group of Year 9 students following the peer-led intervention in experimental schools and following teacher-led sex education in control schools. Focus groups are also undertaken with mixed sex groups of peer educators in the experimental schools. The aim of the focus groups is to gain insight into students’ perceptions and evaluation of sex education i.e. what they liked and disliked, why they thought parts of the sessions were successful or not, how they perceived the peer-educators or teachers as providers of sex education, and their views on wider issues about the school environment and culture. For example, the ways in which staff treat students, the relationship between girls and boys, and the availability and accessibility of welfare support to students.

*Observation*

Key processes in the implementation of the peer-led intervention are observed in all the experimental schools and teacher led sex education is observed in half of the control schools (randomly selected). Observation in the experimental schools includes training meetings with peer educators, in and outside school, and a sample of the peer led sessions with the Year 9 students in each school. For each event, a full description (narrative) is written by the researcher including who was present, what was said, the activities undertaken, interactions between participants, the atmosphere, and the occurrence of significant events such as pupils being dismissed from classrooms. The aim is to gather detailed data on what information was provided, the way in which peers/ teachers delivered the sessions and interacted with the Year 9 students, students' responses, the type of language used, and how the peer-led intervention was implemented.

*Interviews with staff*

Interviews are carried out with staff responsible for sex education and Headteachers in all schools. The aim is to gather information about the content and delivery of sex education, and teachers’ evaluation of it. An additional aim is to identify input from other health-related organisations and services, the extent of teacher training and needs, and how sex education fits within the school curriculum. Information is also gathered about school ethos and the wider context in which sex education is provided. The National Healthy Schools Standard [21] provide a framework for this, highlighting good practice as that which involves parents and carers, the appropriate training and support of school staff and ensuring that the views of the pupils are listened to.

**6 Ethical issues and informed consent**

Consent is sought from parents and Year 9 pupils for participation in the research aspects of RIPPLE, not for the intervention *per se.* This is appropriate because schools can choose to provide peer-led sex education, or not, in the absence of any research study, and parents can choose to withdraw their child from any form of school sex education. The method is as follows: All parents of pupils in Year 9 are sent a letter informing them about the study and asking for their consent. Individual schools can decide whether parental consent will be opt-in (active, signed consent), or opt-out (in which case no expressed objection was interpreted as consent). Year 9 pupils are also given written and oral information about the study before being invited to fill in questionnaires. The researchers explain to pupils that they do not have to fill in the questionnaire if they do not want to. In experimental schools, signed consent is sought from the peer-educators themselves. Consent to take part in RIPPLE therefore amounts to consent for 13-14 year old pupils in all schools to take part in research activities (e.g. filling in questionnaires and taking part in focus groups) and consent from 16-17 year old pupils in the experimental schools to train as peer-educators, deliver sessions to Year 9 pupils and take part in research activities. The study was approved by the UCL/UCLH joint committees on the ethics of human research. School staff and students will receive annual feedback on the progress of the study through a RIPPLE newsletter.

At the time of the 18 month post intervention follow-up, all pupils are asked whether the research team can approach them after they have left school and invite them to continue their participation in the trial. They are asked to indicate their consent by filling in their name and address. Further ethics committee approval will be sought for phase II of the study because it will involve testing for exposure to sexually transmitted infections.

### Plan of analysis

For each of the two primary end points (unprotected sexual intercourse before the age of 16 and termination of pregnancy), the following analyses will be undertaken:

**7.1 School‑level based analyses**

The average annual incidence rates (total number of events divided by total person‑years) in the intervention (R0) and the control (R1) schools will be compared. The observed difference R0 - R1 will be referred to a normal distribution with mean and variance ; where is the true mean annual incidence rate in group i ( i=0,1),, is the person years in school j of arm i, is the total person-years in arm i and k2 is the coefficient of variation between schools in the annual incidence rate. This analysis will be undertaken both unstratified and stratified by the three strata used in the randomisation.

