**4.4 Sample size and power calculations**:

The power calculation takes into account that the school, not the individual, is the unit of randomisation. [20] The number of schools required for the trial depends on 1) the expected incidence rate of the main outcome in the absence of any intervention 2) the variability in the incidence rate between schools 3) the number of participating pupils in each school 4) the magnitude of effect of the intervention that the trial is intended to detect and 5) the desired degree of certainty (statistical power) with which such an effect is to be detected. Termination of pregnancy was chosen as the primary outcome on which to estimate the size of the trial because it is an important and relatively uncommon event for which reliable data are available. Based on the legal abortion rate for 16-19 year olds in England and Wales in 1994 (23 per 1000), the expected cumulative incidence of termination by age 20 will be at least 9%. The variability in outcome between schools can be expressed as k (the coefficient of variation (SD/Mean) of the incidence rate) which, in the absence of reliable data, was assumed to be 0.2. The same variability can also be expressed as a standard deviation of 1.8% which translates into nearly 3 fold variation between schools in the abortion rate from 5% to 13%. With these assumptions, 14 schools, with an average of 150 girls in each, would be needed in each arm to detect a one third reduction in the termination rate, from 9% in control schools to 6% in intervention schools, with over 80% statistical power at 5% significance. However, the value of k, or the extent of between school variability can be reduced by effective stratification of schools (see 4.5 below), thus making the sample size estimates conservative.

The trial will have over 90% power to detect a reduction in the proportion of pupils having unprotected intercourse before age 16, from 35% to 25%, assuming a standard deviation of 8.2% which gives a range of 19% to 51% between schools. Two successive cohorts of Year 9 pupils (with average Year size 150 pupils, or 75 girls) are recruited in each school to provide adequate statistical power. Total number of participants is over 8000.

**4.5 Method of randomisation**.

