**7.2 Analyses based on individual pupil’s outcome**

*Marginal models:*

The marginal probabilty of unprotected intercourse by age 16 and of termination of pregnancy by age 19 will be compared between the intervention and control schools using the Generalized Estimating Equations approach of Liang and Zeger. [22]

*Conditional Models:*

The probability of outcome conditional on school effect will be compared between the intervention and control arms by fitting multilevel methods with random effects for school and cohort using MLwin.

Secondary analyses will adjust the comparisons using marginal models and conditional models for pupil level covariates: sex (first primary endpoint only), ethnic origin, social class etc.

- 1. **Analysis of process data**

Data collected from focus group discussions with students and peer educators, interviews with teachers, observation of lessons and researcher field diaries are transcribed and analysed using a variety of approaches including thematic content analysis and discourse analysis. A particular challenge is to move beyond the usual practice in which 'qualitative' data are analysed separately and sit alongside 'quantitative' measures of outcome. To integrate process and outcome evaluations, qualitative process data are coded to create variables which describe the implementation and acceptability of the intervention. Data on these variables are entered into the computer database and analysed with the data from questionnaire surveys. Data from the process evaluation may also be analysed independently of the data from the questionnaire surveys to generate hypotheses about the importance and impact of local effects on outcomes in individual or groups of schools. The data will also be analysed to address other important questions, for example to describe the type of young people who volunteer to be peer educators and the impact on them of their involvement in the programme.

8 Trial Steering Committee

The trial has a steering committee whose members are:

[name] (Chair), LSHTM

[name], Head of Watford Grammar School

[name], Health Education Co-ordinator, Camden Education Department

[name], R&D Division, Department of Health

[name], MRC Sociology Unit

MRC Observer.

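### Section 7.1 refers the school-level difference to a normal distribution with only 28 randomised schools; if between-school variation is estimated from the trial, the stratified 5% test runs at about 6.3%

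*Protocol*

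**What the plan says.** Section 4.5 randomises 28 schools within three risk strata, 14 to each arm. Section 4.4 sizes the trial on termination of pregnancy. It states that "14 schools, with an average of 150 girls in each, would be needed in each arm" to detect a fall "from 9% in control schools to 6% in intervention schools", "with over 80% statistical power at 5% significance". The between-school coefficient of variation k, "in the absence of reliable data, was assumed to be 0.2". The same section claims over 90% power for unprotected intercourse before 16 (35% against 25%, between-school SD 8.2%) and expects stratification to reduce k.

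For each of the two primary endpoints that it names, section 7 lists three kinds of analysis and does not call any of them the principal one:

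- **School level (7.1).** "The observed difference R0 - R1 will be referred to a normal distribution", with a variance that includes the between-school coefficient of variation. It is done both unstratified and stratified by the randomisation strata.
- **Marginal (7.2).** Arms are compared "using the Generalized Estimating Equations approach". No small-sample correction is mentioned.
- **Conditional (7.2).** A multilevel model is fitted.

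The symbols of the variance expression in 7.1 are not legible in the public text. The legible words do not say whether k is estimated from the trial or set in advance.

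**The concern.** A normal reference is exact only when the variance of the difference is known. Here the between-school part would come from 14 schools per arm. The standardised difference then has heavier tails than the normal, and a cut-off of 1.96 rejects too often. The trial was sized at 5% significance, so a borderline result from 7.1 would carry more false-positive risk than stated, and its confidence interval would be somewhat too short. This is not a detail left open for a statistical analysis plan, because the protocol names the reference distribution.

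**Working it through.** **Inputs.** Sections 4.4 and 4.5: 14 schools per arm; 150 girls per school for termination, 9% against 6%, k = 0.2. For unprotected intercourse: 35% against 25%, SD 8.2%, so k = 0.082/0.35 = 0.234, and two cohorts of 150, so 300 pupils per school. Two-sided testing is assumed, since the protocol does not state it.

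**1. The plan's own figure.** For m pupils per school:

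c = 1 + (1.960 + 0.842)² × [p₁(1−p₁)/m + p₂(1−p₂)/m + k²(p₁² + p₂²)] / (p₁−p₂)²

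For termination the bracket is 0.000546 + 0.000376 + 0.000468 = 0.001390. So c = 1 + 7.849 × 0.001390/0.0009 = 13.1, or 14 schools per arm. The stated figure reproduces. With 14 schools and a normal reference, power is 85.3% for termination and 93.6% for unprotected intercourse.

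**2. True size if the variance is estimated.** Size = P(|t| > 1.960).

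- Unstratified: 28 − 2 = 26 df, size 6.1%, correct cut-off 2.056.
- Stratum as a fixed effect: 28 − 4 = 24 df, size 6.2%, cut-off 2.064.
- Within-stratum, within-arm variances: 28 − 6 = 22 df, size 6.3%, cut-off 2.074.

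**3. Does stratified randomisation change this?** Null trials were simulated, 100,000 per setting, on school proportions. Strata of 9, 9 and 10 schools were assumed, because 28 does not divide by three. Each cell gives termination / unprotected intercourse.

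| Between-school variance explained by strata | Unstratified z | Stratified z | Stratified t, 22 df | Unstratified GEE, robust z |
|---|---|---|---|---|
| 0% | 6.1% / 6.1% | 6.2% / 6.3% | 5.0% / 5.0% | 7.0% / 6.9% |
| 25% | 4.8% / 3.4% | 6.1% / 6.3% | 4.8% / 5.0% | 5.5% / 4.0% |
| 50% | 3.8% / 1.2% | 6.2% / 6.4% | 5.0% / 5.0% | 4.5% / 1.6% |

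Monte Carlo standard error near 6% is √(0.06 × 0.94/100,000), or 0.08 percentage points.

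**4. A variance built as section 7.1 describes** (sampling part plus a k part, unstratified, strata explaining nothing). With k estimated, the size was mostly 5.7-6.2%. The exception is termination with a true k of only 0.1, where it was about 5%. With k known and correct it was 4.8-5.1%.

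**5. If k were fixed at 0.2.** For termination under the null, the variance is proportional to 0.09 × 0.91/150 + k² × 0.0081. This is 0.000627 at k = 0.1, 0.000870 at 0.2 and 0.001275 at 0.3.

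- True k = 0.1: effective cut-off 1.960 × √(0.000870/0.000627) = 2.31, size 2.1%.
- True k = 0.3: effective cut-off 1.960 × √(0.000870/0.001275) = 1.62, size 10.5%.

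**6. GEE.** With equal school sizes the uncorrected robust standard error is too small by √(13/14). The size is then P(|t₂₆| > 1.960 × √(13/14)) = P(|t₂₆| > 1.889) = 7.0%. Simulation without strata effects gave 6.9-7.5%. A √(13/14) correction with t on 26 df gave 4.9-5.5%.

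**7. Power with a t reference** (26 / 24 / 22 df): termination 82.6% / 82.3% / 82.0%; unprotected intercourse 91.8% / 91.6% / 91.4%.

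**The case against.** The strongest reply is that the inflation is conditional. Section 7.1 does not say that k is estimated, and with k known and correct the normal test holds 5%. That stands as a limit on the claim, but it does not rescue the rule: section 4.4 admits that 0.2 had no reliable data behind it, and step 5 shows what a wrong fixed value does.

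A second reply is that stratified randomisation makes the unstratified analyses conservative once the strata matter, and section 4.4 expects them to. That also stands, for the unstratified z-test and for unstratified GEE. It does not help the stratified test, which section 7.1 also prescribes.

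Two stronger readings are tempting.

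- A reader might infer that every primary analysis runs at 6-7%. The upper end comes from GEE without correction, on which section 7.2 is silent. A statistical analysis plan could supply the correction, and the figure needs strata that explain little.
- A reader might also blame "fitting multilevel methods with random effects for school and cohort using MLwin". The trial has two cohorts, so a cohort variance on its own would be poorly estimated. But both cohorts are in every school and in both arms, so a cohort effect cancels from the arm contrast and causes none of the inflation. The wording may also mean cohort within school.

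**Conclusion.** The point holds for the normal reference in section 7.1. With between-school variation estimated from the trial, the stratified test runs at about 6.3% rather than 5% (6.1-6.4% in simulation, with strata explaining 0%, 25% or 50%). The unstratified test runs at about 6.1% only if the strata explain little, and may otherwise be conservative. These figures assume two-sided testing and near-equal allocation within strata. The simulations used school proportions rather than person-year rates.

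The departure is modest. It does not undermine the sample size, and it does not show that intervals are too narrow in every planned analysis. It is a stated rule that does not suit 28 units and is cheap to correct: worth changing, but not a threat to the trial.

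**What to change.** In section 7.1:

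- say that the between-school variance is estimated from the trial, not taken from the planning value;
- take the stratified comparison as the one that matches the randomisation;
- refer it to t on school-based degrees of freedom: 22 with within-stratum, within-arm school variances, or 24 with stratum as a fixed effect. Use 26 for the unstratified version.

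As a linked recommendation, specify for the GEE analysis in 7.2 a bias-corrected sandwich (for example Mancl-DeRouen or Kauermann-Carroll) with t on school-based degrees of freedom.

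The cost in 7.1 is wording and slightly wider intervals: 2.056/1.960 = 1.05 at 26 df and 2.074/1.960 = 1.06 at 22 df. The stated powers of over 80% and over 90% still hold, and no more schools are needed.

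### The randomisation strata are left out of the individual-level models, and the school-level test is run with and without them with no ranking, so precision the design provides may go unused

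*Protocol*

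**What the plan says.** Protocol 4.5 ranks 28 schools on a seven-factor risk score, cuts the ranking into three strata and randomises schools within each.

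Protocol 4.4 sizes the trial on termination of pregnancy, "from 9% in control schools to 6% in intervention schools", "with over 80% statistical power at 5% significance". The between-school coefficient of variation k, "in the absence of reliable data, was assumed to be 0.2". The result is that "14 schools, with an average of 150 girls in each, would be needed in each arm". The section then adds that k "can be reduced by effective stratification of schools (see 4.5 below), thus making the sample size estimates conservative". A second power statement, over 90%, concerns unprotected intercourse before 16, "from 35% to 25%, assuming a standard deviation of 8.2"%.

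The opening of the plan of analysis applies the analyses of 7.1 and 7.2 to each of two primary endpoints and ranks none of them. For the school-level comparison, 7.1 says: "This analysis will be undertaken both unstratified and stratified by the three strata used in the randomisation". In 7.2 the marginal model is a GEE comparison of arms with no covariates named. The conditional comparison is made by "fitting multilevel methods with random effects for school and cohort using MLwin". The secondary versions add covariates at pupil level only. Neither model mentions stratum.

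**The concern.** Stratified randomisation balances the arms on whatever the risk score captures, so the true variance of the treatment comparison is smaller. An analysis without the strata still counts the between-stratum variation as noise. Its standard error is then too large, its confidence interval too wide and its actual type I error below the nominal 5%.

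The protocol itself says that stratification can reduce k, but the estimated standard error reflects this only if the analysis uses the strata. As written, one of the two school-level tests uses them, and none of the models in 7.2 is said to. The stratified and unstratified school-level tests can also fall on opposite sides of 5%, and 7.1 gives no rule for that case.

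**Working it through.** **Inputs.** From Protocol 4.4: 14 schools per arm. Termination is 9% v 6%, with n = 150 girls per school and k = 0.2. Unprotected intercourse is 35% v 25%, with a between-school SD of 8.2%, so k = 0.082/0.35 = 0.234; n = 2 cohorts x 150 = 300 pupils. Significance is 5%, taken as two-sided because 4.4 does not say.

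**Formula.** I used the standard unmatched cluster-trial formula. The variance expression in 7.1 is not legible in the text available.

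- Within-school part: W = p0(1-p0)/n + p1(1-p1)/n
- Between-school part: B = k²(p0² + p1²)
- Total: V = W + B
- Schools per arm: c = 1 + (1.960 + 0.842)² V/(p0-p1)²
- Power: Φ(d/SE - 1.960), with d = p0-p1 and SE = √(V/(c-1))

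**Step 1: the plan's own figures, with no stratification gain.**

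*Termination*
- W = 0.0819/150 + 0.0564/150 = 0.000922
- B = 0.04 x (0.0081 + 0.0036) = 0.000468
- V = 0.001390, of which B is 34%
- c = 1 + 7.849 x 0.001390/0.0009 = 13.12, rounded up to 14
- With 14 per arm, SE = √(0.001390/13) = 0.01034 and d/SE = 2.901, so power = Φ(0.941) = **82.7%**

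*Unprotected intercourse*
- W = 0.2275/300 + 0.1875/300 = 0.001383
- B = 0.0549 x (0.1225 + 0.0625) = 0.010155
- V = 0.011538, of which B is 88%
- SE = √(0.011538/13) = 0.02979 and d/SE = 3.357, so power = Φ(1.397) = **91.9%**

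Both stated figures (over 80% and over 90%) reproduce without any help from the strata.

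**Step 2: strata that explain a fraction f of B.** The documents give no value for f; 10-50% is assumed. The true variance becomes T = W + (1-f)B whichever analysis is used, because the design is stratified either way.

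- A stratified analysis estimates T, so its power is Φ(d/√(T/13) - 1.960).
- An unstratified analysis still estimates V. Its standard error is too large by r = √(V/T), its power is Φ(d/√(T/13) - 1.960r), and its actual type I error is about 2Φ(-1.960r).

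| Endpoint | f | T | r | Power, stratified | Power, unstratified | Type I error, unstratified |
|---|---|---|---|---|---|---|
| Termination | 10% | 0.001343 | 1.017 | 83.9% | 83.1% | 4.6% |
| Termination | 50% | 0.001156 | 1.097 | 88.9% | 84.9% | 3.2% |
| Unprotected intercourse | 10% | 0.010522 | 1.047 | 94.0% | 92.8% | 4.0% |
| Unprotected intercourse | 50% | 0.006461 | 1.336 | 99.4% | 96.9% | 0.9% |

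The effect is larger for unprotected intercourse because B makes up 88% of its variance, against 34% for termination.

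**Step 3: the price of using the strata.** There are 28 - 2 = 26 school-level degrees of freedom, and a three-level stratum term takes two. If the strata explained nothing, termination power by the noncentral t would move from 82.6% (26 df) to 82.3% (24 df).

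**The case against.** The strongest case against the point has five parts.

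- **The sample size does not need the strata.** A reader might infer from 4.4 that the trial counts on stratification and would be underpowered without it. The documents do not support that. The calculation uses the full k = 0.2, and the possible reduction is mentioned afterwards as a reason why the estimate is conservative. This objection stands.
- **A stratified analysis is planned.** A reader might infer that the benefit of stratification is thrown away altogether. It is not, because 7.1 plans a stratified test for each endpoint. This stands too, but it does not reach 7.2 or settle which version in 7.1 counts.
- **The gain is easily overstated.** It is tempting to set 86-89% power (30-50% explained) against 82.7%. But 82.7% applies when the strata explain nothing. The proper comparator at 30-50% is a stratified design analysed without strata, at about 84-85%.
- **The error is in the safe direction.** Omitting the strata inflates no false-positive rate and introduces no bias that the documents show. That is correct; the cost is in precision.
- **Model detail may be in a statistical analysis plan that is not shown.** This carries some weight for the missing stratum term in 7.2. But 7.2 does fix the random effects and the level of the adjusting covariates, and 7.1 shows that the authors had the strata in mind. The two unranked tests in 7.1 are stated, not merely left open.

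**Conclusion.** The point holds as a modest one about unused precision and an unranked pair of tests. The 7.2 models as written do not use the strata that define the randomisation, and 7.1 does not say which of its two tests counts.

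If the strata explain 10-50% of between-school variance, leaving them out costs about 1-4 percentage points of power for termination and about 1-3 for unprotected intercourse. For the latter, confidence intervals could be up to about a third too wide.

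The range for f is an assumption. The score is unweighted and partly based on staff report, so the lower end is plausible. The reproduction also takes k as the same in both arms. If the SD were held equal across arms instead, the baseline power would be 77.9% for termination and 84.1% for unprotected intercourse. That is a question about the planning inputs and would arise whether or not the strata are used. With constant k, ignoring the strata never takes power below the stated 80% and 90%.

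**What to change.** In 7.2, state that every GEE and multilevel model, unadjusted and adjusted, includes stratum as a three-level fixed effect. In 7.1, name the stratified comparison as the one that counts and keep the unstratified version as descriptive only.

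This takes a sentence in each section. It needs no new data, since every school's stratum is known before randomisation, and the sample size in 4.4 can stand as written.
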